### Ethical Considerations

This study was approved by the Conjoint Health Research Ethics Board at the University of Calgary (REB21-0616). Potential participants will be recruited through referral by staff within the clinic. Participants will sign a consent form, which includes study information, procedures, length, potential risks and benefits, confidentiality measures, and information about choosing not to participate or withdrawing from the study with no penalty and no impact on the standard of medical care they receive. Participants receive an electronic gift card as an incentive for participating in this study (CAD $40 [approximately US $30] for completing each assessment). Participant data collected in this study are stored on the Research Electronic Data Capture (REDCap; Vanderbilt University) platform and backed up on the University of Calgary’s secure data storage servers. Data are also stored within the Innowell (Innowell Pty Ltd) platform, which is legally an Alberta Health Services–held repository of patient data that uses encryption to protect data. Data access is limited to clinicians, individual participants, and the research team.

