### Data Analysis

We will use the RE-AIM framework to design and organize the data collection system (Table 3). The *Reach* dimension captures individual outcomes and includes the proportion of stakeholders who take part in the research, complete quantitative and qualitative assessments, and use the additional care options, apps, and e-tools on the Innowell platform. The *Effectiveness* domain also examines individual outcomes and measures changes over time in key outcomes related to mental health (among youth clients), satisfaction with PROMs and stratified care (among clients and clinicians), as well as the use of health care resources (from administrative data). *Adoption* and *Implementation* measure organizational outcomes and so will be more important in later phases of the research when examining how many clinics adopt PROMs and stratified care as well as what are the barriers and facilitators to adoption. *Maintenance* has the longest timescale among RE-AIM dimensions, and it will be used to measure the sustainability of implementation of PROMs and stratified care over time at an organizational and individual level.

This study will begin at the same time as the clinic is implementing stratified care for all clients. For clients who consent to research, PROM results will be used to help inform stratified care, whereas nonresearch participants will be stratified based on clinical judgment alone. The impact of stratified care and implementing PROMs will be inferred from longitudinal changes in client and clinic data, although we cannot control for the impact of other variables changing over time. We will seek a waiver of consent to compare research participants to nonresearch participants, which will provide more direct insights into the impact of using PROMs to inform a stratified care model of mental health service delivery. Analysis will be guided by the three key objectives.

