Improving treatment selection: We will examine changes over time in symptoms for clients at the study clinic. To the extent that implementation of PROMs is leading to continuous improvements in treatment selection as part of an RLHS, we would expect that participants enrolled at the beginning of the study will show slower improvements in their mental health relative to clients enrolled later in the study (as measured by instruments in Table 1). Additionally, if a waiver of consent can be obtained to compare research participants to nonresearch participants, we expect that research participants will show greater improvements in mental health than nonresearch participants when controlling for clinic intake date.Reducing average wait time (prior to service) and treatment duration (once in service): We will examine clinic administrative data to understand whether the implementation of PROMs and stratified care leads to reductions in wait time and treatment duration. If we can obtain a waiver of consent, we will examine whether research participants (completing PROMs using the Innowell platform) spend less time in treatment than those who opt out of research (and do not complete PROMs using the Innowell platform).Increasing the value of services: Clinic administrative data will be used to understand the cost of providing care to each client. When combined with data derived from PROMs, this will provide information about the degree of symptom improvement associated with each type of service. If we can obtain a waiver of consent, we will be able to determine whether the average cost of providing care to a client changes when informed by PROMs. The clinic also seeks to understand the value of services provided to increase cost-effectiveness. By tracking client outcomes associated with each treatment, we can identify which services provide the greatest return on investment.

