## Discussion

### Principal Findings

This protocol paper describes how we will evaluate the implementation of an RLHS to improve service delivery within a stratified model of care. The study clinic is looking for ways to target the right service to the right client at the right time, in line with current movements toward a precision mental health care system [20]. However, standard care at the study clinic has historically been similar to mental health care in most areas of the world, in that, treatment progress is not systematically tracked using objective measures for most clients [19]. Thus, even if the clinic implemented stratified care as a means to tailor services to client needs, the clinic would have no way of knowing if the stratified care model resulted in improved outcomes. Therefore, the clinic needed to develop a platform for PROMs to monitor outcomes to understand the impact of their new stratified care model. Using PROMs to inform stratified care is challenging since there are no existing guidelines to help clinicians understand how scores on different standardized measures translate into treatment recommendations. Therefore, the clinic will need to use an RLHS framework to guide the use of PROMs in informing stratified care decision-making. Initially, stratification using data derived from PROMs (in combination with clinical judgment) may not be superior to stratification using clinical judgment alone. However, as data are collected on how stratification and treatment selection impact the trajectory of a client’s symptoms, the goal is to iteratively improve the ability to stratify clients and select the best treatment plan.

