### Potential Challenges and Limitations

A major uncertainty is the extent to which clinicians will be willing to embrace the use of standardized PROMs to inform decisions about stratified care. Most mental health providers do not use standardized measures and instead rely on their own clinical judgment to determine the best course of care [19]. It will take some time before enough data are collected to allow for past client outcome data to meaningfully inform decisions about future client stratification. The status quo exerts a powerful effect on organizations, and it is common for new mental health initiatives to be abandoned after a few years, especially if there are problems with staff turnover or funding [49,50]. To mitigate these issues, our team spent 3 years building collaborative relationships among researchers, clinic management, and staff through working together on smaller projects, such as a feasibility study of brief transdiagnostic psychotherapy [12]. We are also embedding qualitative and quantitative measures of clinician satisfaction and decision-making throughout the process to identify how we can support clinicians to implement standardized PROMs and stratified care. Another limitation of this protocol is that the decision tree will have limited generalizability to clinics with different patient populations and referral criteria. In the future, we plan to include additional sites to evaluate the approach in other clinical settings serving emerging adults with mental health concerns. Finally, there is the potential bias toward those who contribute the most data [51]. Specifically, emerging adults who consent to completing PROMs and participating in research may not fully represent all patients referred to the clinic. We will evaluate this potential source of bias by analyzing differences between clients who consent to research and those who do based on demographic and clinical variables (eg, diagnoses) available in administrative data.

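### The research versus nonresearch contrasts compare groups formed by staff referral and consent, yet only intake date is named as an adjuster and the difference is read as the impact of PROMs

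*Protocol article*

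**What the plan says.** All references are to the protocol article.

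- **Entry to the study (Ethical Considerations).** "Potential participants will be recruited through referral by staff within the clinic", followed by signed consent.
- **Exposure (Data Analysis).** Clients who consent have their PROM results fed into the choice of stratum; everyone else is placed by clinicians' judgment with no PROM input. The same paragraph presents the comparison of the two groups, subject to a waiver of consent, as the more direct evidence on what PROMs contribute.
- **Symptoms (Data Analysis, first objective).** Research participants are expected to improve more than the other clients "when controlling for clinic intake date". No other adjuster is named.
- **Time in treatment (second objective).** The question is whether research participants "spend less time in treatment than those who opt out of research (and do not complete PROMs using the Innowell platform"). No adjuster is named.
- **Cost (third objective).** With the waiver, "we will be able to determine whether the average cost of providing care to a client changes when informed by PROMs". No adjuster is named.
- **Selection (Potential Challenges and Limitations).** The article accepts that "emerging adults who consent to completing PROMs and participating in research may not fully represent all patients referred to the clinic". It plans to examine differences by consent status on demographic and clinical variables, such as diagnoses, held in administrative data. It does not say that these variables enter the outcome comparisons.

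**The concern.** Exposure to PROM-informed stratification is the same thing as having been referred to the study by staff and having agreed to join. Anything that affects referral or agreement and also affects outcome will appear in the difference between groups. Severity, diagnosis and motivation are obvious candidates. Motivation matters here because the Clinical Setting section makes it a condition of treatment at the clinic.

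Controlling for intake date removes calendar effects such as changes in staffing, services or the stratification process. It removes imbalance in prognosis only as far as that imbalance tracks calendar time.

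At stake is how the results on all three objectives are read. A difference in symptoms, time in treatment or cost that comes from who joined the study could be reported as what PROMs achieved. The cost statement is the firmest, since it says the study will be able to determine the change.

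**Working it through.** **1. The text, side by side.** The article gives no sample size, alpha, power or effect size for these contrasts, so there is no stated figure to reproduce.

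| Contrast | Exposure set by | Adjuster named | How the result is read |
|---|---|---|---|
| Symptoms | referral and consent | intake date | better treatment selection with PROMs |
| Time in treatment | referral and consent | none | shorter treatment with PROMs |
| Cost | referral and consent | none | change in cost when PROMs inform care |

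Two other places show what the authors had available. Phase 4 describes a regression that controls for demographics and social determinants, but it asks whether symptom trajectory differs by stratum, not by research status. The limitations section has demographics and diagnoses to hand for consenters and non-consenters, but uses them to judge representativeness. That step can reveal an imbalance; it does not correct the three contrasts for it.

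**2. Possible size, under assumptions.** None of these inputs is in the documents. Suppose PROMs have no effect and one unadjusted prognostic factor shifts the outcome by g SD. Let its prevalence differ by Δp between groups, unrelated to intake date. Then

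spurious difference = g × Δp.

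With n per group, SE = √(2/n), which is 0.141 at n = 100 and 0.100 at n = 200. The chance that a two-sided 5% test rejects is 1 − Φ(1.96 − bias/SE) + Φ(−1.96 − bias/SE).

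| g (SD) | Δp | Bias (SD) | Rejects, 100 per group | Rejects, 200 per group |
|---|---|---|---|---|
| 0.3 | 0.1 | 0.03 | 5.5% | 6.0% |
| 0.5 | 0.3 | 0.15 | 18.6% | 32.3% |
| 0.8 | 0.4 | 0.32 | 61.9% | 89.3% |

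For the middle row, 0.5 × 0.3 = 0.15. At n = 100, 0.15/0.141 = 1.06, which gives 18.6%. At n = 200, 0.15/0.100 = 1.50, which gives 32.3%.

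At the low end the bias is negligible; at the high end it would dominate the result. A larger sample does not shrink it, and raises the chance of declaring a difference that PROMs did not cause.

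**3. Which variables can be adjusted for.** Phase 2 places the PROMs before assignment to a primary clinician, and Phase 3 uses the results to help set the initial stratum. The stratum is therefore downstream of exposure. Demographics, diagnoses as recorded before consent, and referral source come before exposure and are suitable.

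**The case against.** The strongest reply is that the intake-date clause sits in a sentence stating an expectation, not in a model specification. Nothing says other covariates are excluded, and a condensed article may leave the covariate list to a fuller plan. The comparison depends on a waiver, belongs to an exploratory evaluation within a feasibility study, and is called more direct only relative to the longitudinal inference that the article has just qualified. Consent selection is openly disclosed. The entry criteria, which require a set level of care and motivated clients, also narrow the spread in severity and motivation.

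Much of this stands as mitigation. A reader might infer that the plan rules out every adjuster except intake date; the text does not say that. But the article itself pairs a named adjuster with a reading in terms of impact, and assigns the available variables to a different purpose. Its caveat on uncontrolled variables concerns change over time, not selection into the groups. Entry criteria narrow the spread of prognosis but do not balance it between those who join and those who do not.

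Three stronger readings are tempting and are not supported:

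- **Early leavers.** A reader might infer that clients who leave before being approached count as nonresearch, giving that group short durations and low costs. The duration contrast refers to those who opt out, and nonresearch clients are described as having been stratified. Both point to clients who stayed long enough to be offered a choice and given a stratum.
- **No early benefit.** A reader might take the Discussion to predict none. It says only: "Initially, stratification using data derived from PROMs (in combination with clinical judgment) may not be superior to stratification using clinical judgment alone".
- **An understated average effect.** If the effect rose linearly from 0 to d over uniform intake, a single main effect would estimate d/2. The article states no such model, an average effect over the study is a legitimate target, and the learning hypothesis has its own comparison of earlier with later enrollees.

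**Conclusion.** The point holds. As written, the three contrasts compare self-selected and staff-selected groups, name intake date for one outcome and nothing for the other two, and interpret the result as the impact of PROMs. Planning to describe consent differences does not cure this, because the description is not linked to the outcome comparisons.

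Neither the size nor the direction of the bias can be known from the documents. The range of 0.03 to 0.32 SD rests on one binary factor with assumed strength and imbalance, and the rejection rates also assume equal groups of 100 or 200. Adjustment on administrative variables would reduce the problem, not remove it: motivation and the judgment of referring staff are unlikely to be fully captured. This should be corrected before any data are released under the waiver; it does not undermine the feasibility aims.

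**What to change.** 1. In every research versus nonresearch contrast (symptoms, time in treatment, cost), enter the pre-consent administrative variables that the limitations section already plans to examine, together with intake date. These are demographics and diagnoses, plus referral source if it is available; the article does not list it among those variables. Use them as covariates or through propensity or overlap weights.
2. Do not adjust for initial stratum. PROMs are meant to change it, so conditioning on it would remove part of the effect under study and could add bias.
3. Reword the cost statement to say that the study will estimate the adjusted association between PROM-informed care and cost, and use the same language for symptoms and time in treatment. State that unmeasured motivation and staff judgment in referral remain.
4. Optionally, add a group-by-intake-date interaction as a secondary check of the learning hypothesis. Selection that adds a constant amount over the study would not affect it.

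The cost is some plan wording and a few model terms, using mostly data already intended for analysis. The price is slightly wider intervals and a more cautious claim.

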## Results

This project is funded by the Alberta Children’s Hospital Foundation as one part of a program grant (the “Framework for Research in Emerging Adults”) that is funded from 2021 to 2026. Ethics approval for this study was received in February 2023. Presently, we have developed a system of PROMs and organized clinical services into strata of care. We will soon begin using PROMs to assign clients to a stratum of care and using feedback from youth and clinicians to understand how to improve experiences and outcomes.

## Discussion

### Principal Findings

This protocol paper describes how we will evaluate the implementation of an RLHS to improve service delivery within a stratified model of care. The study clinic is looking for ways to target the right service to the right client at the right time, in line with current movements toward a precision mental health care system [20]. However, standard care at the study clinic has historically been similar to mental health care in most areas of the world, in that, treatment progress is not systematically tracked using objective measures for most clients [19]. Thus, even if the clinic implemented stratified care as a means to tailor services to client needs, the clinic would have no way of knowing if the stratified care model resulted in improved outcomes. Therefore, the clinic needed to develop a platform for PROMs to monitor outcomes to understand the impact of their new stratified care model. Using PROMs to inform stratified care is challenging since there are no existing guidelines to help clinicians understand how scores on different standardized measures translate into treatment recommendations. Therefore, the clinic will need to use an RLHS framework to guide the use of PROMs in informing stratified care decision-making. Initially, stratification using data derived from PROMs (in combination with clinical judgment) may not be superior to stratification using clinical judgment alone. However, as data are collected on how stratification and treatment selection impact the trajectory of a client’s symptoms, the goal is to iteratively improve the ability to stratify clients and select the best treatment plan.

This project has broad implications for mental health care systems as part of a movement toward value-based health care, which is grounded in the notion that compensation for health care services should be based on the amount of benefit to patients rather than the expense incurred by providers and the system [45]. By tracking the relationship between health services and health outcomes, organizations that pay for health care (eg, governments and insurance companies) can obtain an enhanced understanding of which services provide the greatest value for patients at the lowest financial cost [45]. Implementing value-based health care requires a digital platform, patient-centered outcome measurements, tools to support clinical decision-making, and the means to allow for continuous improvement based on data fed into the digital platform [45,46]. An RLHS, such as the one we are implementing and evaluating, leverages these same key components [47] and therefore represents a potentially important first step toward achieving the goal of a value-based health care system [48].

This research will provide practical guidance to help other research and clinical teams collaborate to implement an RLHS as part of the transition toward value-based health care. The engagement of multiple stakeholders early in the design process allowed us to identify the key outcomes that are fundamental toward creating a value-based health care system. Testing out multiple strategies should allow us to identify a system that patients and providers would be willing to use consistently enough to understand which services are having the biggest impact on patient outcomes. Once additional data are generated, we will be able to report on strategies that clinicians use to identify the treatment that is predicted to provide the most value to patients. However, this research protocol focuses on the systematic evaluation of individual outcomes, which is only one component of a value-based mental health care system. At a population level, value-based mental health care also requires additional system-level quality measures including evaluation of structure (eg, number and availability of mental health specialists) and process (eg, number of sessions of psychotherapy) [48].

### Potential Challenges and Limitations

A major uncertainty is the extent to which clinicians will be willing to embrace the use of standardized PROMs to inform decisions about stratified care. Most mental health providers do not use standardized measures and instead rely on their own clinical judgment to determine the best course of care [19]. It will take some time before enough data are collected to allow for past client outcome data to meaningfully inform decisions about future client stratification. The status quo exerts a powerful effect on organizations, and it is common for new mental health initiatives to be abandoned after a few years, especially if there are problems with staff turnover or funding [49,50]. To mitigate these issues, our team spent 3 years building collaborative relationships among researchers, clinic management, and staff through working together on smaller projects, such as a feasibility study of brief transdiagnostic psychotherapy [12]. We are also embedding qualitative and quantitative measures of clinician satisfaction and decision-making throughout the process to identify how we can support clinicians to implement standardized PROMs and stratified care. Another limitation of this protocol is that the decision tree will have limited generalizability to clinics with different patient populations and referral criteria. In the future, we plan to include additional sites to evaluate the approach in other clinical settings serving emerging adults with mental health concerns. Finally, there is the potential bias toward those who contribute the most data [51]. Specifically, emerging adults who consent to completing PROMs and participating in research may not fully represent all patients referred to the clinic. We will evaluate this potential source of bias by analyzing differences between clients who consent to research and those who do based on demographic and clinical variables (eg, diagnoses) available in administrative data.

